### Data collection

Sociodemographic (age, sex, educational level, marital and working status), anthropometric (height and weight to calculate the body mass index) and general clinical data (long-term oxygen, non-invasive ventilation, medical history, comorbidities to calculate the Charlson Comorbidity Index [45] and medication) will first be collected with a structured questionnaire to characterise the sample and will be followed by a lung function test with spirometry [46].

The primary outcome measure will be health-related quality of life, assessed with the St. George Respiratory Questionnaire (SGRQ) [47] in patients and with the World Health Organization Quality of Life Bref Questionnaire [48, 49] in caregivers. The number of acute exacerbations, healthcare utilisation costs and collateral costs (e.g. transport costs, work absence costs, sickness benefits) will also be collected to conduct the cost-benefit analysis [50].

In addition, the following secondary outcomes will be assessed: symptoms of dyspnoea (modified Medical Research Council Questionnaire [mMRC]) [51], fatigue (Checklist of individual strength [CIS-20]) [52] and Functional assessment of chronic illness therapy – fatigue [FACIT-F]) [53, 54], cough and sputum (Leicester cough questionnaire [LCQ] [55] and Cough and sputum assessment questionnaire [CASA-Q]) [56], impact of the disease (COPD Assessment Test [CAT]) [57, 58], emotional status (The Hospital Anxiety and Depression Scale [HADS]) [59, 60], Family Adaptation and Cohesion Scales [FACES-IV]) [61, 62], peripheral (biceps and quadriceps with the hand held dynamometer, 1 [1-RM] or 10 [10-RM] repetition-maximum) [63, 64] and inspiratory and expiratory muscle strength (respiratory pressure meter) [65], exercise capacity (six-minute walk test [6MWT] and one-minute sit to stand test [1-min STS]) [66, 67], balance (brief-balance evaluation systems test [Brief-BESTest]) [68] and physical activity (accelerometer) [14]. Peripheral muscle (rectus femoris and biceps brachialli) and diaphragm thickness, cross sectional area [69, 70] and echointensity [71], excursion and M-Mode Index of Obstruction (MIO) [72–74], will be measured with ultrasound images – ImageJ and Matlab software. Global rating of change scale [75] for fatigue, cough, sputum, peripheral and respiratory muscle strength and balance will also be collected.

Data will be collected from patients and caregivers at baseline, at 12 weeks and at 3- and 6-months post-PR. Ultrasound imaging will only be collected at baseline and at 12 weeks in patients from the experimental group. Additional file 2 provides an overview of enrolment, intervention and outcomes to be assessed in each time point.

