## Methods

### Aims

The main goal of this project is to implement an innovative community-based PR programme and assess its cost-benefit. The primary objectives are to:1.1.Investigate the short- and medium-term effects of community-based PR programmes, implemented with minimal resources and with local healthcare professionals, in patients and caregiver’s health-related quality of life;1.2.Investigate the cost-benefit of the community-based PR programmes on acute exacerbations and healthcare utilisation, to determine whether the intrinsic perceived social value of such programmes have identifiable benefits and, consequently, measurable economic value for society.

The following secondary objectives will be addressed:2.1To explore the short- and medium-term effects of community-based PR programmes on patients and caregivers’ symptoms, impact of the disease, family adaptability/cohesion, peripheral and respiratory muscle strength, exercise capacity, balance and physical activity.2.2To explore differences between patients and caregivers’ who participate and those who did not participate in community-based PR programmes in relation to dyspnoea, fatigue, cough, impact of the disease, emotional state, health-related quality of life, number of exacerbations, healthcare utilization, family adaptability/cohesion, peripheral and respiratory muscle strength and thickness, exercise capacity, balance and physical activity.2.3To explore associations between patients and caregivers’ outcomes of dyspnoea, fatigue, cough, impact of the disease, emotional state, number of exacerbations, healthcare utilisation, family adaptability/cohesion, peripheral and respiratory muscle strength and thickness, exercise capacity, balance and physical activity, pre-post community-based PR programmes.2.4To investigate the short-term effects of community-based PR programmes on patients’ peripheral muscle (quadriceps and biceps) and diaphragm thickness, cross sectional area, echointensity and motion measured resorting to ultrasound imaging.

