### Sample size

A sample size estimation with 80% power at 5% significance was calculated to detect significant differences in patients’ health-related quality of life assessed with the SGRQ. The pre-post score achieved in the intervention group of a PR in COPD integrating family-based education and psychosocial support was used (Pre 37.9 ± 18.2 vs. Post 31.4 ± 18.7, *p* < 0.001) [27], resulting in a total sample size of 73 participants. In PR programmes, dropout rates are approximately 20 to 40% [89, 90]. Therefore, 102 participants will be recruited. Sample size calculation was performed using G*Power 3.1.3 (Universität Düsseldorf, Düsseldorf, Germany).

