### Data management and statistical analysis

All variables will be processed in IBM SPSS or MS Excel software. Descriptive statistics, including frequencies, means and standard deviations, medians and interquartile ranges, will be used as appropriate. Short- and medium-term effects of the community-based PR programmes will be verified using paired t-test or Wilcoxon signed-rank tests, accordingly to data normality. Mean scores of continuous variables will be compared between patients and their caregivers using independent samples t-test or Mann Whitney U test, depending on the variable distribution. Pearson correlation coefficient [91] and Bland and Altman plots [92] for continuous variables and Cohen’s k [93] for categorical variables, will be applied to study the relationship and agreement between patients and caregivers. Relationships between variables will be explored with inferential, correlational and univariate/multivariate analyses in SPSS. Differences between the EG and CG at different time points will be assessed using a two-way ANOVA with repeated measures (continuous data), Kruskal-Wallis (ordinal data) and Chi-square or Fisher exact probability tests (nominal data). If missing data is found during the study follow up, the generalized estimating equation’ models will be applied. This method is an extension of generalized linear models to longitudinal data which permits the inclusion of time-dependent variables and the analysis of incomplete data (without imputing missing data), common in longitudinal health studies [94]. A significance level of 0.05 will be used.

Whenever possible, minimal clinically important differences (MCID) will be established, following the current recommendations to integrate both anchor-based and distribution-based approaches [95, 96]. The final MCID for each measure will be pooled using MetaXL 5.3 (EpiGear International, Queensland, Australia), with the input data being the MCID generated by each anchor- and distribution-based method and, when appropriate, the respective confidence interval. A quality effects model [97] will be used and anchor-based methods will weigh more than distribution methods (i.e., 2/3 against 1/3) [98].

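### The primary quality-of-life outcome spans two instruments, two populations and several visits, with no deciding visit, instrument or success rule, while the sample size covers only one of these contrasts

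*Protocol article*

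**What the plan says.** Under Data collection the article says "The primary outcome measure will be health-related quality of life, assessed with the St. George Respiratory Questionnaire (SGRQ" and continues "in patients and with the World Health Organization Quality of Life Bref Questionnaire" for caregivers. One primary outcome is thus measured by two instruments in two sets of people.

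Objective 1.1 under Aims is to "Investigate the short- and medium-term effects of community-based PR programmes" on the quality of life of both patients and caregivers. The schedule is "Data will be collected from patients and caregivers at baseline, at 12 weeks and at 3- and 6-months post-PR", which gives three visits after baseline.

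Under Data management and statistical analysis, "Short- and medium-term effects of the community-based PR programmes will be verified using paired t-test or Wilcoxon signed-rank tests". Experimental and control groups are compared by a two-way repeated-measures ANOVA for continuous outcomes, with generalized estimating equations if data are missing. On error control the section says only "A significance level of 0.05 will be used".

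Under Sample size, "A sample size estimation with 80% power at 5% significance was calculated" for patients' SGRQ alone. It uses the before and after scores of the intervention group in a previous family-based rehabilitation study, and gives 73.

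**The concern.** Which endpoint is primary, in whom and when, is a matter for the protocol itself. Here the primary outcome and primary objective spread over two populations and several visits, and nothing says which result settles the question.

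The visits also ask different things. Twelve weeks measures the effect at the end of the supervised programme; the later visits measure whether it lasts. A gain at 12 weeks that is gone six months after the programme has no agreed reading, nor has a gain in patients without one in caregivers.

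The error rate and the power both depend on the missing rule. If any one result is enough, the 5% level does not hold for the primary claim as a whole. If both instruments are needed, the power statement covers only half of the claim.

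**Working it through.** **Inputs from the article.** Level 0.05 (two-sided assumed; sidedness is not stated); two primary instruments; three post-baseline visits; SGRQ 37.9 ± 18.2 before and 31.4 ± 18.7 after; 80% power; N = 73. **Assumed, because the article gives none:** the correlation between visits and the correlation between patient and caregiver.

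**1. What the sample size covers.** For a paired t-test the standardised change is 6.5 / √(18.2² + 18.7² − 2r·18.2·18.7), where r is the before-after correlation.
- With r = 0.44 the SD of the change is 19.53 and the standardised change is 0.333. Two-sided 5% and 80% power then need 73.
- With r = 0.43 the answer is 75, and with r = 0.45 it is 72.

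The stated 73 therefore fits a single paired SGRQ contrast in patients, with an unstated r near 0.44.

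It does not fit a between-group comparison. For a difference of 6.5 and an SD of 18.45 (the mean of the two SDs), the number per arm is 2 × (1.96 + 0.842)² × 18.45² / 6.5² ≈ 127, or 128 with the t distribution.

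**2. Any one result counts, one overall test per instrument.** This matches the repeated-measures ANOVA. If independent, 1 − 0.95² = 9.75%. With patient-caregiver correlation 0.3 it is 9.5%, and with 0.5 it is 9.1% (simulation, 1,000,000 draws).

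**3. Any one result counts, six separate tests.** This is the paired-test reading: two instruments at three visits. If independent, 1 − 0.95⁶ = 26.5%. Simulation of six correlated two-sided z tests gives:

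| Between-visit correlation | Patient-caregiver correlation 0 | Patient-caregiver correlation 0.5 |
|---|---|---|
| 0.5 | 23.6% | 22.0% |
| 0.7 | 20.6% | 19.2% |
| 0.8 | 18.7% | 17.4% |
| 0.9 | 16.0% | 14.9% |

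The independent figure is best read as a ceiling, because all changes share one baseline. With equal variance σ² and equal correlation ρ between all pairs of visits, two changes have covariance σ²(1 − ρ) and variance 2σ²(1 − ρ), so they correlate 0.5.

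SGRQ alone at three visits gives 14.3% if independent, 12.6% at correlation 0.5 and 9.9% at 0.8.

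**4. Both instruments must succeed at one named visit.** The chance of a false joint claim is at most 5%. The article gives no power for caregivers. If it were also 80% (assumed), joint power would be 0.8 × 0.8 = 64% if independent. It cannot fall below 0.8 + 0.8 − 1 = 60% and reaches 80% only if the two tests always succeed together.

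**The case against.** A reader might infer that the trial's false positive rate simply is about 18-26%. The documents do not support that as a fact. It needs six separate tests, a rule that any one of them suffices, and between-visit correlations of about 0 to 0.8; none of these is stated. The between-group analysis is one repeated-measures model per outcome, which gives about 9-10% over the two instruments. Even with six tests, 18% is not a floor: a correlation of 0.9 gives 15-16%.

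It can also be said that the lead contrast is plain enough, since the sample size rests on patients' SGRQ before and after the programme. That does point to 12 weeks, but the article never calls this contrast primary, and objective 1.1 and the outcome definition say something wider.

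Patients and caregivers are different people, and treating claims about them as one error family is a convention that can be disputed. If they are kept apart, SGRQ with separate tests at three visits still gives about 10-14% for correlations of 0.8 down to 0.

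Finally, this is a condensed article. Additional file 2 is not shown, and an analysis plan may set out how multiplicity is handled. The absence of a multiplicity procedure is therefore no fault here. What stands is narrower: the article itself defines the primary outcome and objective so widely that no deciding endpoint can be read from them.

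**Conclusion.** The point holds as a defect in how the primary endpoint is fixed. The article names two primary instruments in two populations, makes short- and medium-term effects both primary, and applies 0.05 throughout without a deciding visit, instrument or success rule. Its power statement covers one contrast only.

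The size depends on the missing rule:
- Any one result suffices: about 9-10% with one overall test per instrument (patient-caregiver correlation 0 to 0.5), or about 15-26% with six separate paired tests (between-visit correlation 0.9 down to 0). The correlations are assumptions.
- Both instruments must succeed at a named visit: no inflation, but the joint claim has no stated power.

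No single error rate can be attributed to the plan as written. The change should be made; it is a matter of definition and does not call the data collection into question.

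**What to change.** Name one primary endpoint: change in patients' SGRQ total score from baseline to 12 weeks. State in the same sentence which comparison is tested. Either it is the change within the experimental group, which is what the sample size covers, or it is the difference in change between experimental and control groups. The stated power does not carry over to the second, so choosing it means recalculating the sample size.

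Then either test the later SGRQ visits and one named caregiver WHOQOL-Bref score in a fixed, pre-set order, each at 0.05 and only while every earlier test succeeds, or label them secondary and report them with confidence intervals. The order is for the sponsor to choose.

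The cost is about one paragraph of wording. Naming the endpoint needs no extra data or patients, apart from the recalculation above if the between-group test is chosen. The downside is that caregiver and follow-up effects can be claimed as confirmed only if the tests before them succeed.

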### Intervention

A 12-week community-based PR programme will be implemented in primary healthcare centre with minimal resources (i.e., pulse oximeters, blood pressure monitors, modified Borg scales, chairs, stairs, corridors, free weights built with bottles with sand when others are not available, elastic bands and cushions). Healthcare professionals from each primary healthcare centres will receive two sessions of training, of three to 4 hours each, prior to starting the programme. These sessions will focus on how to assess patients’ comprehensively, main modules to approach in the education and psychosocial components and importance of involving a multidisciplinary team. Physiotherapists will also revise principles of exercise safety, prescription and patients’ monitoring. The PR programme will then be implemented in collaboration with members of the research team, who are highly experienced professionals in running PR. When the programmes finish, local healthcare professionals will continue to implement programmes by themselves and the research team will be available for assistance and clarification of doubts by phone.

The programme will be composed of pre/post PR comprehensive assessment of patients and caregivers, two weekly sessions of exercise training and one session of education and psychosocial support every other week. Caregivers of the EG will be invited to participate in these sessions that will be delivered in group, but personalised to each patient/caregiver.

Each exercise session will last between 60 and 75 min and will be delivered by an experienced physiotherapist in accordance with the international guidelines [28], i.e., it will include warm up, aerobic, resistance and balance training and a cool down period. Furthermore, inspiratory muscle training [65] will be provided if maximal inspiratory pressure is < 80 cmH_2_O [76]. Heart rate and oxygen saturation (with a pulse oximeter) and perceived dyspnoea and fatigue (with the modified Borg scale) [77], will be monitored throughout the sessions. Intensity of the aerobic and resistance training will be individually prescribed using the 6MWT [66] and the 1-RM or 10-RM methods [64] (considering the availability of the local equipment), respectively. After a 5 min. Warm-up period (range-of-motion, stretching, low-intensity aerobic exercises and breathing techniques), aerobic training will be conducted in corridors and stairs/steps or in cycloergometers or treadmills if available in the facilities, for 20–30 min at 80% of the average speed achieved during the 6-MWT, or 60 to 80% of their work peak, or 60 to 80% of maximum heart rate [40, 78]. Resistance training will consist of 8 exercises of the major upper and lower limb muscle groups, at 60 to 70% of 1-RM or tailored in accordance to the 10-RM, using free weights and ankle weights for 20–25 min [79]. A balance training component will follow for 10 min with exercises for the six subsystems of balance control [80] and then the programme will finish with a 5 min. Cool down period. During the PR programme, progression in the training intensity will be tailored according to the perceived dyspnoea and fatigue (4–6 in the modified Borg scale). A detailed description of the exercise training component can be found in Fig. 1.

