**Methods:**

A 12-week community-based PR will be implemented in primary healthcare centres where programmes are not available. Healthcare professionals will be trained. 73 patients with CRD and their caregivers (dyads patient-caregivers) will compose the experimental group. The control group will include dyads age- and disease-matched willing to collaborate in data collection but not in PR. Patients/family-centred outcomes will be dyspnoea (modified Medical Research Council Questionnaire), fatigue (Checklist of individual strength and Functional assessment of chronic illness therapy – fatigue), cough and sputum (Leicester cough questionnaire and Cough and sputum assessment questionnaire), impact of the disease (COPD Assessment Test), emotional state (The Hospital Anxiety and Depression Scale), number of exacerbations, healthcare utilisation, health-related quality of life and family adaptability/cohesion (Family Adaptation and Cohesion Scale). Other clinical outcomes will be peripheral (biceps and quadriceps-hand held dynamometer, 1 or 10 repetition-maximum) and respiratory (maximal inspiratory and expiratory pressures) muscle strength, muscle thickness and cross sectional area (biceps brachialis, rectus femoris and diaphragm-ultrasound imaging), exercise capacity (six-minute walk test and one-minute sit to stand test), balance (brief-balance evaluation systems test) and physical activity (accelerometer). Data will be collected at baseline, at 12 weeks, at 3- and 6-months post-PR.

Changes in the outcome measures will be compared between groups, after multivariate adjustment for possible confounders, and effect sizes will be calculated. A cost-benefit analysis will be conducted.

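### Rehabilitation is delivered in groups at several centres, but the sample size and named tests treat patients as independent; if SGRQ change is correlated within groups, the experimental group's pre-post standard error is too small

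*Protocol article*

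**What the plan says.** The Abstract (Methods) sets the programme in more than one centre: "A 12-week community-based PR will be implemented in primary healthcare centres where programmes are not available". Under Study design, setting and recruitment, each centre identifies its own team. Under Intervention, staff of each centre are trained before the programme starts, aerobic equipment and the strength-testing method depend on what the site has, and the sessions are collective: "Caregivers of the EG will be invited to participate in these sessions that will be delivered in group, but personalised to each patient/caregiver". Controls receive standard care from the primary healthcare team, with no group sessions.

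The Sample size section states: "A sample size estimation with 80% power at 5% significance was calculated to detect significant differences". Its input is a single-group change, "Pre 37.9 ± 18.2 vs. Post 31.4 ± 18.7", "resulting in a total sample size of 73 participants". The only inflation, to 102, is for dropout ("dropout rates are approximately 20 to 40"%). No group size, number of centres, ICC or design effect appears.

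Data management and statistical analysis assigns paired t or Wilcoxon tests to the programme's effects over time. Differences between experimental and control groups "will be assessed using a two-way ANOVA with repeated measures (continuous data), Kruskal-Wallis (ordinal data") and chi-square or Fisher tests (nominal data). Generalized estimating equations (GEE) are kept for the case of missing data and described as a longitudinal method. None of these is given a centre or PR-group term. The Abstract promises multivariate adjustment for possible confounders without listing them.

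**The concern.** Patients in one PR group share a physiotherapist, a timetable, the site's equipment, the education team and each other's company. The SGRQ is self-reported. Groups may therefore differ in how much their members improve, and two patients from one group would then carry less information than two patients from different groups. A paired t-test on individual patients ignores this.

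At stake are the validity of the pre-post test on the primary outcome and the power figure that justifies 73. That figure is built on exactly this pre-post change. The issue is more than a detail left to an analysis plan, because the article itself fixes a sample size, a power and a list of tests, and all of them assume independence.

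**Working it through.** **Inputs from the article.** Mean change 37.9 − 31.4 = 6.5; SDs 18.2 and 18.7; 80% power; 5% significance; n = 73. I take 73 as the number analysed in the experimental group, as the Abstract does ("73 patients with CRD and their caregivers (dyads patient-caregivers) will compose the experimental group").

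**Inputs assumed.** Two-sided test; pre-post correlation r; patients per PR group m = 8 to 10; ICC of the *change* score 0.01 to 0.05. The article gives none of these.

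**1. Reproducing 73.** SD of change = √(18.2² + 18.7² − 2·r·18.2·18.7), standardised change dz = 6.5 / SD of change, and power comes from the noncentral t with n − 1 degrees of freedom.

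| r | SD of change | dz | n for 80% | power at 73 |
|---|---|---|---|---|
| 0.40 | 20.22 | 0.322 | 78 | 77% |
| 0.44 | 19.53 | 0.333 | 73 | 80% |
| 0.50 | 18.46 | 0.352 | 66 | 84% |
| 0.60 | 16.51 | 0.394 | 53 | 91% |

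So 73 is consistent with a paired t-test on independent patients at r of about 0.44, a value the article does not state. Solving for exactly 80% at 73 gives dz = 0.332, which is used below.

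**2. Adding clustering of change.** Design effect DE = 1 + (m − 1)·ICC; effective n = 73/DE; the unadjusted standard error is too small by the factor √DE; true two-sided error of the nominal 5% test = 2·[1 − Φ(1.96/√DE)].

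| m | ICC | DE | effective n | power | √DE | true error |
|---|---|---|---|---|---|---|
| any | 0 | 1.00 | 73 | 80% | 1.00 | 5.0% |
| 8 | 0.01 | 1.07 | 68.2 | 77% | 1.03 | 5.8% |
| 10 | 0.01 | 1.09 | 67.0 | 76% | 1.04 | 6.0% |
| 8 | 0.05 | 1.35 | 54.1 | 67% | 1.16 | 9.2% |
| 10 | 0.05 | 1.45 | 50.3 | 64% | 1.20 | 10.4% |

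Here power is computed at the effective n with effective n − 1 degrees of freedom. With 73/10 ≈ 7 to 73/8 ≈ 9 groups, a proper cluster analysis has far fewer degrees of freedom, which would lower power further.

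**3. Sensitivity to r.** At r = 0.50, 73/66 = 1.11, so a design effect up to about 1.1 still leaves 80%. At DE = 1.07 power is 82%; at DE = 1.45 it is 69%.

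**4. Experimental versus control.** Clustering by PR group exists in one arm only. If controls come from the same centres, shared centre effects partly cancel in the difference. The two forces oppose each other, and without the number of centres and the mix of arms within them their net effect cannot be computed.

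**The case against.** The strongest reply is that no harm is demonstrated. The article gives no ICC, and at the low end of the assumed range the loss is a few points of power. Training intensity is individually prescribed, content is tailored, staff in all centres get the same training, and the Discussion says an experienced team member attends every session. All of this limits differences between groups. Stable differences between centres in SGRQ level cancel in a pre-post comparison, so only correlated change matters. These points stand, and they make the finding conditional. They do not supply a reason to assume an ICC of zero.

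A second reply is that GEE and the promised confounder adjustment cover the matter. They do not. As described, GEE handles repeated measures within a patient and only when data are missing. Adjusting for confounders would not correct standard errors for correlated response within PR groups.

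Three stronger readings are tempting but unsupported:

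- *True power is below 80%.* The article omits the pre-post correlation, and at r = 0.50 a small design effect is absorbed. The supportable statement is that power is lower than under independence.
- *The standard error of the controlled comparison is too small.* This does not follow, for the reason in step 4 of the working.
- *Centre confounds the comparison.* Arms are formed by willingness, with matching on age and disease only, so this is possible. But nothing shows that the mix of arms differs by centre, and the unlisted confounders may include it.

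**Conclusion.** The concern holds in conditional form. Group delivery at several centres is part of the design, and neither the sample size nor any named test allows for it. For the experimental group's pre-post SGRQ analysis, any positive within-group correlation of change makes the standard error too small, by about 3% to 17% of its true value over the assumed range (1 − 1/1.03 to 1 − 1/1.20). Power of about 77% to 64% and a true error of about 6% to 10% rest on three assumptions: 8 to 10 patients per group, an ICC of 0.01 to 0.05, and 80% power at 73 under independence, which itself needs r of about 0.44. For experimental versus control the direction and size are open. The point is worth correcting because the correction is cheap.

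**What to change.** 1. **Pre-post analysis, experimental group.** Replace the plain paired test on the primary outcome with a mixed model, or a cluster-robust analysis of change, with PR group as the cluster. Use a small-sample correction, since groups are likely to be few.
2. **Experimental versus control.** Adjust for centre, and use a partially nested model with a PR-group random effect on change in the experimental group only. Keep centre and PR group distinct. PR group must not be a fixed effect: controls have no PR group, so such terms would be aliased with treatment. A random intercept for centre alone absorbs differences in level but not clustering of response to the programme.
3. **Sample size section.** Say that 80% power assumes no clustering. Give the planned group size and number of centres, and the power at one or two ICC values.
4. **Reporting.** Report the estimated ICC of change.

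This changes wording and analysis only; it needs no new data or patients beyond recording which PR group each patient attended. The price is somewhat wider intervals.
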